### Study participants

The study participants will comprise Middle Eastern students in early adolescence, within the ages of 13 and 14 years, located in Arabic schools in the Klang Valley area. The inclusion criteria include Arabic students aged 13 to 14 years, with at least one parent consenting to their participation in this study. Students afflicted with illnesses such as asthma, diabetes, cancer, cardiovascular diseases, fractures, cirrhosis, or other diseases, as well as students exempted from physical activities due a medical condition, will be excluded from this investigation. The sampling unit will be represented by a randomly selected Arabic school Middle Eastern adolescent, who meets the inclusion and exclusion criteria set for this study.

### Ethical approval and informed consent

Ethical approval for the RCT was obtained from the Ethics Committee for Human Study of Universiti Malaya (UM) [UM.TNC2/UMREC_2039], and the directors of the selected schools. Written consent will be acquired from all parents, or the legal guardian, of the participants. Also, the participants, and their parents, will be privy to a description of the study, through an information sheet. The information provided covers: the purpose and procedures of the study, the unrestricted right of a participant to withdraw from the study, and the data collection process at three time periods (baseline, post-line, and two months after post-line). The participants and their parents, will be given the opportunity to inquire about the research, before extending their consent. Participants will be assured, that their participation in the study is entirely voluntary, and that they have the unrestricted right, to withdraw from the study at any time.

### Sample size

The cluster randomized control trial formula was applied to calculate the sample size, taking into consideration a power of 80%, and a 95% confidence level [28]. According to the proportion of overweightness among adolescents, calculated in a previous study conducted by James et al. [29]:

$$n=DE\times (Z_{1‐\alpha /2}+Z_{1‐\beta })\frac{2P1(1-P1)+P2(1-P2)}{(P1-P2)2}$$

DE = 1+ *p* (m-1)

**where**:

Z_1-α/2 =_ Standard score for (1–0.025) = 1.96Z_1-β =_ Standard score (1–0.20) = 0.84 (80% power)P1 = The proportion of those overweight from control group (p1) = 27.6%P2 = The proportion of those overweight from Intervention group (p2) = 23.1%Intra-cluster correlation (*P*) = 0.05Number of individuals in each cluster (m)DE = Design Effect = 2.2

$$n=2.2\times (1.96+0.84)\;\frac{20.276(1-0.276)+0.231(1-0.23)}{(0.276-0.23)2}$$

Sample size = 220

Adding 15% to the number of subjects as attrition rate = 250

Therefore, the total sample size is 250 participants (125 participants for each group).

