### Study setting

Conducted in Arabic schools located in the Klang Valley, this study involves students in grades seven and eight. There are a total of 25 Arabic schools in the Klang Valley, an urban region in Malaysia, with its centre in Kuala Lumpur. Excel software will be used for the random selection and allocation of 4 out of these 25 Arabic schools. The first two schools are assigned intervention groups, while the next two are assigned control groups. Subsequently, 4 classes will be randomly selected from each school. Two of these classes will consist of 13-year-old seventh-grade students, while the next two will consist of mostly 14-year-old eighth-grade students.

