### Sampling method

Simple random sampling will be used for the selection of participants. Two schools will be assigned the intervention group, and two schools the control group, followed by the selection of classes. With this form of probability sampling, researchers use a sampling frame, which includes a list of all students from the selected schools. For this study, a table of random numbers, will be used for the selection of participants, up to the point the sample size is attained. The random selection of participants is achieved by way of Excel software.

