**Fig 2 pone.0289937.g002:**
[figure not shown]
Consort 2010 flow diagram.

*Randomization*. Randomization is ensured throughout the study, using sealed opaque envelopes. An independent researcher places envelopes enclosing the names of the schools in a box, and randomly selects four envelopes to represent the intervention and control schools. The independent researcher uses Excel software, for the selection of the participants. For this selection process, the IDs of all students will be entered into the datasheet, a random column will be created, and the formula " = RAND()" will be applied. Respondents will be assigned a unique code, for the allocation of a concealment mechanism. This is to circumvent individual-level bias.

*Intervention*. ‘Healthy lifestyle’ intervention is based on the HBM theory, which considers the attitudes and beliefs of adolescents, for the development of their skills and favourable behaviours. A team of health promotion experts, from the University of Malaya’s department of social and preventive medicine, with a special interest in obesity-related behaviour alteration, will assist the researcher, during the designing of the educational health promotion program.

The intervention is specifically designed to:

Provide adolescents with the facts, statistics, and harmful effects, linked to obesity and overweightness.Encourage the consumption of healthy diets, to keep the risks of obesity at bay.Promote the indulgence in physical activity, to reduce the risks of obesity.Inspire students to adopt positive health behaviours.Develop a good decision-making and self-care attitude.Develop the three health belief elements of perceived susceptibility, perceived threat, and perceived benefit vs. barriers.

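### The stated design effect of 2.2 implies 25 pupils per cluster, but four randomised schools share 220 to 250 pupils, which gives 3.7 to 4.1 if the ICC of 0.05 is a school-level value.

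*Protocol article*

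**What the plan says.** The Sample size section sets out a cluster-trial formula, "taking into consideration a power of 80%, and a 95% confidence level". Its design effect is 1 + ICC × (m − 1), with an intra-cluster correlation of 0.05. It names m as the number of individuals per cluster, gives it no value, and then states "DE = Design Effect = 2.2". The remaining inputs are "The proportion of those overweight from control group (p1) = 27.6"% and "The proportion of those overweight from Intervention group (p2) = 23.1"%. The result is 220, raised to 250 for 15% attrition, or 125 per group.

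Three places describe the clusters:

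- Study setting: "Excel software will be used for the random selection and allocation of 4 out of these 25 Arabic schools", and then "Subsequently, 4 classes will be randomly selected from each school".
- Sampling method: "Two schools will be assigned the intervention group, and two schools the control group, followed by the selection of classes".
- The Randomization paragraph: an independent researcher "randomly selects four envelopes to represent the intervention and control schools".

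**The concern.** In a cluster trial, m in the design effect is the number of analysed pupils who share one allocation. Here that is the number per school. The printed 2.2 fixes m once the ICC is given, and the value it fixes can be compared with the schools and pupils that the article describes. They do not agree.

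This figure is the only allowance for clustering in the sample-size calculation. If it is too small, any power or precision statement built on it is too favourable, and that remains so after the other errors in the calculation are put right. An analysis that adjusts for clustering, as the planned GEE does, aims at an honest standard error. It does not recover the information that the plan counted on.

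**Working it through.** **Inputs.** ICC = 0.05, DE = 2.2, 220 pupils before and 250 after the attrition allowance, 27.6% v 23.1% (Sample size); 4 schools and 4 classes per school, so 16 classes (Study setting); 2 schools per arm (Sampling method).

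**Cluster size implied by 2.2.** m = (2.2 − 1)/0.05 + 1 = 25.

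**Cluster sizes in the design**, assuming equal sizes:

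| Unit | Pupils | m | DE = 1 + 0.05 × (m − 1) |
|---|---|---|---|
| School (4) | 220 | 55 | 3.70 |
| School (4) | 250 | 62.5 | 4.075 |
| Class (16) | 220 | 13.75 | 1.64 |
| Class (16) | 250 | 15.625 | 1.73 |

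Neither level gives 2.2. Sixteen classes of 25 would be 400 pupils.

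**Size of the understatement.**

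| | 110 per arm | 125 per arm |
|---|---|---|
| DE for schools | 3.70 | 4.075 |
| Shortfall, 1 − 2.2/DE | 41% | 46% |
| Effective n per arm at DE 2.2 | 110/2.2 = 50 | 125/2.2 = 57 |
| Effective n per arm at school DE | 110/3.70 = 30 | 125/4.075 = 31 |
| SE ratio, √(DE/2.2) | 1.30 | 1.36 |

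**Detectable difference for a continuous score.** The article gives none, so this is an illustration: one time point, no covariate adjustment, 80% power, two-sided 5%, in units of the total SD. The standard error of the difference is √(2 × DE/n):

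- 110 per arm: √(2 × 3.70/110) = 0.259
- 125 per arm: √(2 × 4.075/125) = 0.255

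The normal approximation multiplies by 1.96 + 0.84 = 2.80, giving 0.73 and 0.71 SD. At DE 2.2 it would give 2.80 × √(2 × 2.2/110) = 0.56 and 2.80 × √(2 × 2.2/125) = 0.53 SD.

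With two schools per arm, however, there are only 4 − 2 = 2 between-school degrees of freedom. The t quantiles are 4.303 (97.5%) and 1.061 (80%), which sum to 5.364. This gives 5.364 × 0.259 = 1.39 SD and 5.364 × 0.255 = 1.37 SD. The noncentral t on 2 df needs a noncentrality of about 5.65, which gives 1.47 and 1.44 SD. Roughly 1.4 SD is the usable figure.

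**Does the corrected design effect lead back to 220?** No. The standard two-proportion formula for 27.6% v 23.1% is (1.96 + 0.84)² × (0.276 × 0.724 + 0.231 × 0.769)/0.045² = 7.84 × 0.3775/0.002025, about 1,461 per arm before clustering (1,466 with the pooled variance). From the pooled figure, the totals are 2 × 1,466 × 2.2 ≈ 6,450, 2 × 1,466 × 3.70 ≈ 10,848 and 2 × 1,466 × 4.075 ≈ 11,948. Without squaring the z sum, as the formula is printed, the result at DE 2.2 is about 1,148. None of the literal readings tried gives 220 or 110.

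**The case against.** **The value 4.1 is not established as the true design effect.** A reader might infer that it is. The article does not say at which level, or for which outcome, the 0.05 was estimated. An implied m of 25 could be an assumed class size; the school-level ICC would then be unknown rather than 0.05. Power also rests on the pupils expected to remain, 220, which gives 3.7. This objection stands in part. What survives is the inconsistency, with a conditional range of 3.7 to 4.1. A class-level reading does not rescue 2.2, because classes are chosen within schools already assigned and because 16 classes do not give 25 pupils each.

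**Pupils might be the unit allocated.** The recruitment paragraph speaks loosely of allocating participants. The Study setting, Sampling method and Randomization text all assign schools, and a design effect would have little purpose otherwise. This does not stand.

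**The detectable difference might be read as 0.71 SD instead of 0.53 SD.** That contrast uses normal quantiles and ignores the 2 degrees of freedom. It should not be used: four schools can detect about twice 0.71 SD on the stated assumptions.

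**Correcting the design effect alone repairs nothing.** This is true. The 220 is not reproducible, and its proportions concern overweight while the primary outcome is the KAP questionnaire. The point is still separate, because a recalculation for either outcome would need a design effect and 2.2 would carry the error into it.

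**The trial might be thought to need ten schools.** Ten schools of 25 pupils would match 2.2 and give 8 degrees of freedom. That is a change of design with more sites to approve and staff, and nothing in the article shows it to be feasible. It does not follow from the inconsistency.

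**Conclusion.** The point holds as an inconsistency among printed figures, so it is not a matter of detail that an article leaves to a fuller document. At an ICC of 0.05, the value 2.2 belongs to clusters of 25, and neither the schools nor the classes of this design have that size. With schools as clusters the design effect is 3.7 on 220 pupils and 4.1 on 250.

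These values assume that 0.05 is the school-level ICC and that schools contribute equal numbers; unequal numbers would raise them further. The 1.4 SD figure assumes in addition an unadjusted comparison at one time point. Adjustment for baseline could improve it by an amount that the article gives no means of estimating. The error concerns planned precision and is not evidence that the effect estimate will be biased.

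**What to change.** In the Sample size section:

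1. State m as pupils per school: 55 expected for analysis, 62.5 recruited.
2. State that the ICC of 0.05 is at school level, and for which outcome. If it is not a school-level value, supply one and recompute.
3. Replace the design effect of 2.2 with 3.7 (4.1 on 250 pupils).
4. Restate the power or detectable difference with t quantiles on 2 degrees of freedom for two schools per arm. On the present inputs this is roughly 1.4 SD for a continuous score at 80% power.
5. Make these changes together with the correction of the sample-size formula, since a new design effect inserted into the present calculation would still not support 220.

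This costs a recalculation and a few lines of text, with no change to conduct. It will show plainly how little four schools can detect.

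Spreading the same pupils over more of the 25 schools would lower the design effect and add degrees of freedom. It is optional and costs more: further school directors' agreement, more sites for the researcher who delivers the sessions, and a new look at the plan for four classes per school (25 pupils over four classes is about 6 each).

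### Enrolling 250 covers a 12% loss from 220, not the stated 15%; a minor slip to correct together with the base number

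*Protocol article*

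**What the plan says.** The calculation is in the Protocol article, Materials and methods, Sample size. It aims at a design "taking into consideration a power of 80%, and a 95% confidence level" and ends with "Sample size = 220". The attrition step follows directly: "Adding 15% to the number of subjects as attrition rate = 250". The conclusion is that "the total sample size is 250 participants (125 participants for each group"). Because 250 is called the total, 220 must also be a total, or 110 per arm.

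Two other sections bear on the step. Sampling method says pupils are drawn until the sample size is reached, and describes no reserve beyond it. Statistical analysis says missing values are not replaced and that the outcomes at three time points are analysed by GEE. The article gives no other attrition figure and no other reason for 250.

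**The concern.** An attrition allowance exists so that the required number is still there after the expected loss. The step has two faults, and both push enrolment down. First, 250 is less than the stated operation yields. Second, the operation itself is too small: the 15% is lost from those enrolled, so the required number has to be divided by 0.85. Multiplying it by 1.15 falls short.

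At exactly the loss the plan allows for, the trial would finish below the number it calculated. The rule would also carry over to any recalculation, where the same relative error costs more pupils.

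**Working it through.** **Inputs**, all from the Sample size section: required number 220 in total; attrition 15%; enrolled 250, or 125 per arm.

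**1. The plan's own figure.** Adding 15%: 220 × 1.15 = 253. The plan states 250, which is 3 pupils or 1.2% lower. That is close enough to be rounding, but it rounds a minimum down. The increase actually made is 250/220 − 1 = 13.6%.

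**2. The number that keeps 220 after a 15% loss.** n/(1 − d) = 220/0.85 = 258.8, so 259, or 260 for two equal arms of 130.

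**3. What 250 delivers.**
- Remaining after a 15% loss: 250 × 0.85 = 212.5, or 106.25 per arm against 110.
- Shortfall: 220 − 212.5 = 7.5 pupils, or 3.4% of 220.
- Loss that 250 covers in full: 1 − 220/250 = 12.0%.

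**4. How the shortfall divides.** Enrolling 253 would leave 253 × 0.85 = 215.05, so adding instead of dividing accounts for about 4.95 pupils. The step from 253 down to 250 accounts for 3 × 0.85 = 2.55. Together they make 7.5.

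**5. Cost in power, on the supposition that 220 gives 80%.**
- If information falls in proportion to pupils, 106.25 per arm against 110 gives about 78.6%, a loss of about 1.4 points.
- If pupils are lost within a fixed set of clusters, the design effect falls too. The stated "DE = Design Effect = 2.2" with an intra-cluster correlation of 0.05 implies m = 1 + 1.2/0.05 = 25. After the loss, m = 25 × 212.5/220 = 24.1 and the design effect is 1 + 0.05 × 23.1 = 2.16. The effective number goes from 220/2.2 = 100 to 212.5/2.16, about 98.5, and power is about 79.4%.

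The range is therefore 78.6% to 79.4%, or about 79%.

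**6. Whether 220 is a valid starting point.** The inputs are "The proportion of those overweight from control group (p1) = 27.6"% and "The proportion of those overweight from Intervention group (p2) = 23.1"%, with z-values of 1.96 and 0.84. The usual formula gives, per arm:

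(1.96 + 0.84)² × (0.276 × 0.724 + 0.231 × 0.769)/0.045² = 7.84 × 0.3775/0.002025, about 1,461.

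Multiplied by 2.2 this is about 3,215 per arm, or about 6,430 in total. A figure near 220 appears only if the first variance term is doubled and the difference in proportions is multiplied by 2 instead of squared: 2.2 × 7.84 × 0.5773/(0.045 × 2) = 110.6 per arm. At 110 per arm with a design effect of 2.2, power for 27.6% against 23.1% is about 7%.

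**7. The same rule on a recalculated base.** With 6,430 as an illustration, 6,430 × 1.15 = 7,395 (rounded up) and 6,430/0.85 = 7,565. Adding instead of dividing would leave enrolment about 170 pupils too low.

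**The case against.** There is a fair case that this hardly matters.

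- **Rounding.** The article names its operation, which gives 253, and 250 splits neatly into two arms of 125. A gap of 1.2% may be casual rounding. This stands, so the 3 pupils alone should not be called a calculation error.
- **The aim is implied.** The article never says that 220 will remain after a 15% loss. That is true, but an allowance labelled as attrition has no other purpose, and 250 meets that purpose only up to a 12% loss.
- **Partial data.** A pupil who misses only the two-month visit can still contribute earlier observations to the GEE. About 212 is therefore the number with complete follow-up and close to a worst case for the information available.
- **The target is itself unsound.** Falling from 220 to 212 has little meaning when 220 does not follow from the stated proportions. This stands as a limit on importance. It does not make the attrition step right, and the rule would be reused when the base is recalculated.

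A reader might infer that the attrition step is what deprives the trial of its stated power, or that enrolling 259 would restore it. The document supports neither reading. The step costs at most about 1.4 points even if 220 is granted, and the large deficit comes from the base number.

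**Conclusion.** The point holds as a minor error. The plan presents 250 as 220 with a 15% attrition allowance, but 250 is 13.6% above 220 and covers a 12% loss. At 15% attrition about 212 pupils, about 106 per arm, have complete follow-up, which is 7 to 8 fewer than 220. Keeping 220 would take 259.

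The power figure of about 79% instead of 80% is conditional on 220 being valid for 80% power, which the stated inputs do not support. It also treats a lost pupil as contributing nothing. The arithmetic on 220, 250 and 15% needs neither assumption.

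**What to change.** Reword the attrition line in the Sample size section without enrolling more pupils. Either of these would do:

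- *Enrolling 250 pupils allows for 12% attrition relative to a figure of 220.*
- *At 15% attrition, 250 enrolled pupils leave about 212 with complete follow-up (about 106 per arm).*

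Wherever the sample size is recalculated, divide the required number by (1 − 0.15) instead of multiplying it by 1.15, and round up to equal arms.

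Make this edit together with the correction of the base number, and do not let the new sentence present 220 as a sound requirement for 80% power. The attrition edit costs wording only, and the stated allowance becomes slightly less favourable.

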### Study outcomes

#### Primary outcome

The knowledge, attitude, and practice of nutrition and physical activity questionnaire (KAP-Q) will be used, to measure the primary outcome of interest for this study, in accordance with the approach employed by Sharif Ishak et al. [31] and Harake et al. [32]. The questionnaire consists of 73 items: knowledge (30), attitude (22), and practice (21). The knowledge section serves to determine the participants’ level of comprehension, regarding nutrition and physical activity. The response options to the multiple-choice questions in the questionnaire are ‘True’, ‘False’ and ‘I do not know’. Correct responses will be designated ‘1’, while incorrect and ‘I do not know’ responses will be designated ‘0’. The maximum score is 30, and the minimum 0. A score above the mean is an indication of good knowledge. The five Likert scale responses for assessing attitude are ‘strongly agree’, ‘agree’ ‘neutral’, ‘disagree’, and ‘strongly disagree’. Eleven negatively termed questions will be inversely recoded during data analysis. The maximum score is 110, and the minimum 22. A higher score is an indication of a greater positive attitude. The practice section includes 21 questions, which come with five Likert scale responses: ‘very frequently’, ‘often’, ‘sometimes’, ‘rarely’, and ‘never’. Nine negatively termed questions will be inversely recoded during data analysis. The maximum score is 105, and the minimum 21. A higher score is an indication of a more positive practice.

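### The sample size of 220 (250 with attrition) and its 80% power do not follow from any valid use of the plan's own inputs, and the calculation is not on the primary outcome

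*Protocol article*

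**What the plan says.** All inputs are printed under Sample size in the protocol article. The calculation is made "taking into consideration a power of 80%, and a 95% confidence level", and it rests on overweight: "According to the proportion of overweightness among adolescents, calculated in a previous study". The listed values are 27.6% overweight in the control group, 23.1% in the intervention group, standard scores of 1.96 and 0.84, an intra-cluster correlation (ICC) of 0.05 and a design effect of 2.2. No value is given for the cluster size m. The stated result is 220, followed by "Adding 15% to the number of subjects as attrition rate = 250" and then "Therefore, the total sample size is 250 participants (125 participants for each group").

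Under Primary outcome, the KAP questionnaire "will be used, to measure the primary outcome of interest for this study". Change in BMI, with its weight categories, is listed under Secondary outcome. Study setting assigns four schools, two to each arm.

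**The concern.** A difference of 4.5 percentage points between two proportions near 25% is small. Even individually randomised trials need well over a thousand participants per arm to detect it, so 220 looks wrong on sight. If it is wrong, the article claims 80% power that the design lacks for the only comparison it was sized on. A reader would then take a null result on overweight as informative when it would say almost nothing.

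The second problem is independent of the first. Even a correct calculation on overweight would not show that the trial is large enough for the KAP questionnaire.

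**Working it through.** **Inputs (Sample size).** P1 = 0.276, P2 = 0.231, difference 0.045, z-values 1.96 and 0.84, ICC 0.05, DE 2.2. From Study setting: four schools, two per arm.

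**Trying to reproduce 220.** The standard formula per arm is n = DE × (1.96 + 0.84)² × [P1(1−P1) + P2(1−P2)] / (P1−P2)².

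- Variance term: 0.276 × 0.724 + 0.231 × 0.769 = 0.19982 + 0.17764 = 0.37746.
- Squared difference: 0.045² = 0.002025.
- No clustering: 7.84 × 0.37746 / 0.002025 = 1,461 per arm.
- With DE 2.2: 2.2 × 1,461.4 = 3,215 per arm, or 6,430 in total.
- With P2 rounded to 0.23, as the worked line does in places: 3,072 per arm.

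The figure of 220 is not reproduced, whether read as a total or per arm. One near-match exists. Treat the loose 2s in the printed formula as multipliers, so that P1(1−P1) is doubled and the difference is doubled instead of squared: 2.2 × 7.84 × [2 × 0.19982 + 0.17764] / (2 × 0.045) = 110.6 per arm, or 221 in total. That is not a valid sample size formula. Whether it is what was done cannot be known from the article.

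**Power for the overweight difference at the planned size.** SE = √(DE × 0.37746 / n per arm). Power = Φ(0.045/SE − 1.96) + Φ(−0.045/SE − 1.96).

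| Cluster basis | n per arm | DE | SE | Power |
|---|---|---|---|---|
| Stated DE (implies m = 1 + 1.2/0.05 = 25) | 110 | 2.2 | 0.0869 | 8.1% |
| Stated DE | 125 | 2.2 | 0.0815 | 8.6% |
| Schools, m = 55 | 110 | 1 + 0.05 × 54 = 3.7 | 0.1127 | 6.8% |
| Schools, m = 250/4 = 62.5 | 125 | 1 + 0.05 × 61.5 = 4.075 | 0.1109 | 6.9% |
| No clustering | 110 | 1 | 0.0586 | 12.0% |
| No clustering | 125 | 1 | 0.0550 | 13.0% |

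These values include the small chance of a significant result in the wrong direction. Without it, the clustered values are about 0.6 to 0.9 points lower.

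More pupils in the same four schools would not help. With two schools per arm and ICC 0.05, the effective sample size cannot exceed 2/0.05 = 40 per arm. At that limit SE = √(0.37746/40) = 0.097 and power is about 7.5%.

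**Outcome.** No KAP difference or standard deviation is given, so KAP power cannot be calculated. As an illustration only, assume that ICC 0.05 also applies to a KAP score and that there are 62.5 pupils per school:

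- SE of the difference = √(2 × 4.075/125) = 0.255 SD.
- Detectable at 80% power, normal approximation: 2.80 × 0.255 = 0.71 SD.
- With a t reference on 2 degrees of freedom (four schools minus two arms): (4.303 + 1.061) × 0.255 = 1.37, about 1.4 SD.

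Neither figure allows for any gain from baseline adjustment or repeated measures.

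**Attrition.** 220 × 1.15 = 253, and 220/0.85 = 259. Conversely, 250 × 0.85 = 212.5, which is below 220.

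**The case against.** The best defence concerns legibility. The printed formula has 2s in odd places: before P1, inside what reads as 20.276, and after the bracketed difference. These are most likely superscripts displaced in conversion. A reader might infer that the authors forgot to square the sum of the z-values. The article does not support that, because the stray 2 before P1 is plausibly that very exponent. The objection stands, and no criticism of the formula's typography is made here. It does not rescue the result, since the inputs are also listed in plain text and the correctly squared formula gives 3,215 per arm.

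A reader might also infer that 220 is a per-group figure mislabelled as a total. This is not shown. The article does not say which it is at that step, and the near-match above (110.6 doubled) would make it a total.

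A third tempting inference is that the trial has only about 8% power for its primary outcome. It does not follow. That figure is for overweight alone and comes from the arithmetic, not from the choice of outcome. The trial may be able to detect a large KAP effect; the article simply does not show it.

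Nor does the 8% say anything about BMI-for-age z-scores, which are also planned. BMI is already secondary, so nothing here requires relabelling it.

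Finally, the attrition gap is small. Adding 15% and rounding 253 down to 250 is a common simplification. That is fair, and the point is minor.

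**Conclusion.** The concern holds on two separate counts.

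1. The stated 220 and 80% power are wrong for the stated inputs. The required size is about 3,215 per arm at DE 2.2, roughly 26 times the planned 125 (3,215/125 = 25.7). Actual power for 27.6% versus 23.1% is about 8% at the stated design effect and about 7% with schools as clusters. Dropping clustering altogether raises it only to 12–13%, so the conclusion does not depend on the design effect.
2. The calculation does not address the KAP questionnaire, so the 80% figure has no support for the primary outcome.

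The first count rests only on figures printed in the article and a normal approximation. The school-level power also takes the stated ICC of 0.05 to apply between schools, with equal school sizes. The KAP figures of 0.7 and 1.4 SD are illustrations: they borrow that ICC, and the second uses a t reference that the plan does not state. The attrition discrepancy is real but minor.

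**What to change.** Keep 250 participants and rewrite the Sample size section:

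- Withdraw the 80% power claim and the statement that 220 results from this formula and these inputs.
- State the actual power for the overweight difference, about 7–8%, and name the cluster size behind it (25, or 62.5 per school). Use the same cluster basis throughout the section.
- Replace the justification with the difference in the KAP score detectable with four schools, two per arm. State the assumed ICC, the reference distribution and any allowance for baseline adjustment. At ICC 0.05 and 62.5 per school, the illustration is about 0.7 SD by normal approximation and about 1.4 SD with t on 2 degrees of freedom.
- Correct the attrition line. Either give about 212 analysable after 15% loss from 250, or state the roughly 12% loss (30/250) that leaves 220.

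The cost is wording only, with no added participants or schools. The downside is that the stated power becomes much less favourable, and the authors must say openly that the trial cannot settle the overweight question.
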